# Case management after acquired brain injury compared to care as usual: study protocol for a 2-year pragmatic randomized controlled superiority trial with two parallel groups

**DOI:** 10.1186/s13063-020-04804-2

**Published:** 2020-11-17

**Keywords:** Brain injury, Stroke, Traumatic brain injury, Caregivers, Case management, Transitional care, Psychosocial, Early intervention, Family, Randomized controlled trial

## Abstract

**Background:**

People with acquired brain injury may suffer from cognitive, emotional and behavioural changes in the long term. Continuity of care is often lacking, leading to a variety of unmet needs and hindering psychosocial functioning from the occurrence of brain injury up to years thereafter. Case management aims to prevent (escalation of) problems and to facilitate timely access to appropriate services. In other populations, case management has shown to improve psychosocial well-being. In this study, we aim to evaluate the feasibility of case management after acquired brain injury and its effectiveness and cost-effectiveness, compared to care as usual.

**Methods:**

This is a pragmatic randomized controlled superiority trial with two parallel groups and repeated measures in adults with ABI and their family, taking place between November 2019 and December 2021 in three provinces in the Netherlands. Participants will be randomly allocated to either the case management group, receiving case management from hospital discharge up to 2 years thereafter, or the control group, receiving care as usual. Effectiveness will be evaluated every 6 months for 18–24 months by patient-reported psychosocial well-being (Hospital Anxiety and Depression Scale (HADS), Utrecht Scale for Evaluation of Rehabilitation-Participation (USER-P) restriction subscale and the Life Satisfaction Questionnaire (LiSat)), self-management (Patient Activation Measure (PAM)) and care needs (Longer-term Unmet Needs after Stroke (LUNS)). Family outcomes include self-efficacy (Carer Self-Efficacy Scale (CSES)), caregiver burden (Caregiver Strain Index (CSI)), psychosocial well-being (LiSat, HADS), family needs (Family Needs Questionnaire (FNQ)). Feasibility will be evaluated using qualitative methods, assessing fidelity, dose delivered, dose received, reach, recruitment and context. Cost-effectiveness will be determined by the EQ-5D-3L and service use.

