### Eligibility criteria {10}

#### People with ABI

People with ABI are eligible for the trial if they comply with all of the following criteria at hospital discharge:
Acquired brain injury objectified by medical specialist (meningitis, encephalitis, hydrocephalus, subarachnoid hemorrhage, intracerebral or intracranial hemorrhage, ischemic stroke, transient ischemic attack, concussion, contusion, other head trauma).Aged 18 years or older.Living in the community prior to the injury.Discharged home or to a rehabilitation centre after hospital visit/admission.Sufficient command of the Dutch language to understand study procedures.Access to a computer and the internet (to use the monitoring tool, see ‘Intervention description {11a}’).Willing and able to give informed consent.

Exclusion criteria for people with ABI are:
A neurodegenerative disorder such as Parkinson’s disease or dementia (because of the progressive course of the disease).A diagnosis related to neuro-oncology (since an intensive care trajectory is already in place for this group).Discharge to a nursing home.

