### Who will take informed consent? {26a}

People with ABI and family members who are willing to participate will be visited at home by a trained research assistant, who will obtain informed consent prior to baseline assessment and after going over the study procedures. In case the home visit cannot take place, study procedures will be explained over the phone and informed consent is obtained by mail.

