### Intervention description {11a}

#### Case management

##### The framework

The framework for case management for ABI was developed based on a combination of the taxonomy for case management [24] and descriptions of case management for dementia in the Netherlands (e.g. [33–46]), because this form of case management is reasonably well integrated in the Dutch health care system. Such services can serve as a base for care innovations for people with ABI because of the shared focus on supporting people to adapt to the consequences of a disorder or disease in daily life [47].

Case management aims to support people with ABI and family member’s’ self-management of the consequences of ABI and psychosocial well-being, to prevent (escalation of) problems and to facilitate timely access to appropriate services. We propose the following case management elements:
Monitoring: tracking functioning and well-being of people with ABI and family members. In the present study, a digital monitoring system is used for this purpose (described below).Identification: identification of questions, problems and needs (based on monitoring) that hinder functioning and well-being at the time they emerge.Assessment: assessing the nature and severity of the presented problem, burden on and capabilities of the person with ABI and the family member, the role of their social network, making implicit or unmentioned questions and problems explicit, drawing conclusions about the core problem in the individual context.Information (psycho-education): providing information and education on the (impact of) ABI to assist understanding, information or education related to the question or problem (with a focus on capabilities to self-manage the problems), informing on available care and support services.Provision of support: guiding decision-making with regard to managing the problem, providing practical or psychosocial support for relatively mild problems (focused on maintaining or improving self-management).Referral: referring to more specialized care or support for relatively complex problems and guiding decision-making with regard to what available services to use.Coordination: supporting access to services, facilitating collaboration between different service providers and bringing about appropriate care when this is not available through the regular services.

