People with ABI and family members, each having their own account, will automatically receive an email every 3 months, which allows them to enter the monitoring system and to answer two questions: (1) Do you experience problems as a consequence of brain injury? (2) Are you (Is your loved one) able to do all the things you were (he/she was) doing prior to the brain injury? Both questions can be answered with yes or no. If the participant responds ‘yes’ to question 1 and/or ‘no’ to question 2, they are directed to a 32-item questionnaire asking about functioning in the areas of health, daily life, activities, social contacts and consequences of ABI. This questionnaire was composed by the developer of the ReMinder (authors KHMJ and MD), inspired by the Checklist for Cognitive and Emotional Consequence of Stroke (CLCE-24 [48]), the Utrecht Scale for Evaluation of Rehabilitation-Participation (USER-P [49];), Outcome Questionnaire (OQ-45 [50];) and the life domains of the ICF: International Classification of Functioning, Disability and Health (ICF-model). Participants fill out the questionnaires as self-report. Family members fill out the questionnaire reporting about the person with ABI and five extra questions about his or her own well-being. In order to facilitate easy access to the case manager, at completion of the 32-item questionnaire participants will be asked if they would like to have contact with the case manager (yes/no). In addition, people with ABI and family members also have the opportunity to ask a question to the case manager directly at any time within the online environment.

The responses are visible to the case manager to keep track of functioning and well-being of the person with ABI. The case manager will contact those participants who explicitly indicate that they would like to get in touch. For participants who do not initiate contact with their case manager themselves, the case manager determines whether to contact the participant after the second time participants have filled out the ReMinder (i.e. 3 months after the first ReMinder questionnaire). The decision to get in touch with the participant will generally be based on whether responses indicate that certain problems have not been resolved (consistently low scores in one or more areas), a deterioration in scores, or profound discrepancies in scores between the person with ABI and their family member.

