### Recruitment {15}

At each of the three recruiting hospitals, trained hospital staff will select eligible people with ABI from the electronic patient files. The hospital staff explains the aim of the study and the study procedures to the patient and ask whether they have a family member who might be interested in participating as well. When the person with ABI or person with ABI-family-member couple is interested in participation, the hospital staff will send them the study information and notifies the researcher. The researcher will call after a week to clarify any questions patients or family members may have. If they are interested in participating, an appointment will be scheduled with the research assistant to sign informed consent, complete the baseline assessment and perform the randomization. In case the person with ABI is referred to inpatient rehabilitation, the appointment will take place as soon as possible after discharge.

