#### Effectiveness and cost-effectiveness

The baseline assessment will be completed no more than 2 months after the visit to or discharge from the hospital or, in case of inpatient rehabilitation following hospital discharge, as soon as possible after they leave the rehabilitation centre. Ideally, assessments take place at the participants’ home, but can take place via telephone or questionnaires may be sent and returned by mail in case home visits are not possible (on time). A trained research assistant will explain the study procedures once more and collect the consent form. During home visits, participants fill out the questionnaires on their own and have the opportunity to ask questions. The research assistant will provide support when necessary, for example by reading the questions and possible answers out loud in case of reading difficulties (a common problem after stroke). Information on gender, educational level and living situation will be collected at baseline; date of birth, type and date of most recent and previous brain injuries and discharge destination will be drawn from hospital records by hospital staff. Follow-up measurements will be mailed to the participants, unless people prefer to be assisted, in which case a research assistant (blind to treatment allocation) will visit them at home.

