## Statistical methods

### Statistical methods for primary and secondary outcomes {20a}

#### Effectiveness

Multilevel modelling will be used to assess the improvement of case management participants over time compared to care as usual. Primary analysis involves entering time, group and their interaction (exposure) as fixed terms. Separate analyses will be performed to assess 24-month outcomes for the subgroup of participants for whom this data is available. Sensitivity analysis will be performed by extending the resulting models with covariates, controlling for the effects of age, gender and level of education. Covariates will be kept in the model as long as they contribute significantly to the model. Significance of the fixed regression effects will be tested using the appropriate *t*-test (*α* = .05).

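### The abstract starts case management at hospital discharge, but allocation follows a later baseline visit: define the start as randomisation and adjust for when month 0 falls

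*Protocol article*

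**What the plan says.** The Methods part of the abstract states that the intervention group is "receiving case management from hospital discharge up to 2 years thereafter". The Discussion motivates the trial by the lack of a chain of support that begins at discharge.

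The body of the protocol describes a different start:

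- **Eligibility criteria {10}:** "People with ABI are eligible for the trial if they comply with all of the following criteria at hospital discharge".
- **Who will take informed consent? {26a}:** those willing to take part "will be visited at home by a trained research assistant, who will obtain informed consent prior to baseline assessment". Telephone and mail are the fallback.
- **Recruitment {15}:** the researcher telephones a week after the information has been sent, and only then is the appointment made. "In case the person with ABI is referred to inpatient rehabilitation, the appointment will take place as soon as possible after discharge".
- **Plans for assessment and collection of outcomes {18a}, Effectiveness and cost-effectiveness:** "The baseline assessment will be completed no more than 2 months after the visit to or discharge from the hospital". For inpatient rehabilitation, baseline follows the end of that stay, with no limit in time.
- **Implementation {16c}:** the allocation envelope is opened once baseline is complete.
- **Outcomes {12}:** assessments are at baseline and at 6, 12, 18 and 24 months.
- **Statistical methods {20a}, Effectiveness:** the primary model has time, group and their interaction. A sensitivity analysis extends it by "controlling for the effects of age, gender and level of education", and a covariate stays only while it is significant. Sample size {14} adds that baseline measures enter the model.
- **Other study parameters (under Outcomes {12}):** injury date, length of hospital stay and discharge destination are recorded.

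**The concern.** The stated start of the intervention is one that the design cannot deliver. If the abstract's wording carries into the conclusions, clinicians and payers will read the result as the effect of support that begins on leaving hospital. What is randomised is an offer made later, to people who have reached a post-discharge or post-rehabilitation visit.

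The same procedures make month 0 a mixed point. The eligibility list runs from transient ischaemic attack and concussion to intracerebral haemorrhage, and people who go through inpatient rehabilitation are included. For one participant baseline may come soon after a brief hospital visit. For another it comes after a hospital stay and a full rehabilitation stay. Recovery proceeds at different rates at these stages, which can add spread to the HADS trajectories. None of the three covariates named for the model describes the stage of recovery.

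**Working it through.** **1. Order of events.** Set side by side, the sections give one sequence: hospital discharge (eligibility judged), information sent, telephone call a week later, appointment, consent, baseline, envelope opened. Allocation is last. With D the time from hospital discharge to allocation:

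- discharged home: D is more than 0 and at most 2 months;
- inpatient rehabilitation: D = L + w, where L is the length of the rehabilitation stay and w the wait after it. The article gives neither a value nor a cap for either.

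No route gives D = 0, which is what the abstract's wording requires.

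**2. Where the assessments fall.** Time since discharge at an assessment = D + assessment month.

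| Assessment | Discharged home | After rehabilitation |
|---|---|---|
| Baseline | just over 0 to 2 months | L + w |
| 6 months | just over 6 to 8 months | 6 + L + w |
| 18 months | just over 18 to 20 months | 18 + L + w |
| 24 months | just over 24 to 26 months | 24 + L + w |

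The same model time thus covers a spread of up to 2 months among those discharged home, and a spread with no stated bound once rehabilitation patients are included.

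**3. Is the comparison biased?** No. Time from injury and discharge destination are fixed before the envelope is opened, so randomisation balances them in expectation. The effect of the timing is on what is estimated and on residual variance.

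**4. Size of the possible precision gain.** The plan's own arithmetic comes first, taking its 194 as given: 194 × (1 − 0.5²) = 145.5, rounded up to 146; 146 / (1 − 0.30) = 208.6, rounded up to 209. Both match the plan, and neither depends on the timing.

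The implied HADS standard deviation is 3.25 / 0.36 = 9.03. After adjustment for baseline with R = 0.5 it is 9.03 × √0.75 = 7.82.

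The documents do not say how much of the remaining variance the two timing variables explain. Assume 2% to 5% and apply the plan's own 1 − R² factor again:

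- 2%: 146 × 0.98 = 143.1, about 3 participants; residual SD 7.82 × √0.98 = 7.74;
- 5%: 146 × 0.95 = 138.7, about 7 participants; residual SD 7.82 × √0.95 = 7.62.

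The gain is small but nearly free.

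**The case against.** The best defence is that only one clause in the abstract is loose. The methods state the real timing openly, and the objectives do not mention the discharge transition. The trial is pragmatic and its inclusion is deliberately broad, so varied recovery stage is part of the design. Baseline HADS already absorbs some of the differences. Length of hospital stay is used for exploratory subgroups, and the missing-data sensitivity analysis may bring in recorded variables. Further covariates are often left to an analysis plan, which is not shown here.

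Much of this stands: there is no bias, and the precision gain is probably small. But the abstract does contradict the methods. The article also names its covariate set and a retention rule based on significance, so this is a choice that the article has fixed.

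Three stronger readings are tempting, and the documents do not support them.

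- **That the discharge transition is not tested at all.** Two months is a maximum. People discharged home may be allocated within weeks, and from then on they can ask for contact or put a question to the case manager at any time.
- **That the 6-month HADS largely reflects monitoring alone.** For participants who do not initiate contact, "the case manager determines whether to contact the participant after the second time participants have filled out the ReMinder", 3 months after the first. That is 3 months after allocation if the first ReMinder comes at entry, or 6 months if it comes 3 months later; the article does not say which. But no contact rate is given, contact on request is open earlier, and monitoring is itself a listed element of case management.
- **That the framework contradicts the ReMinder rule.** The framework speaks of identifying problems "that hinder functioning and well-being at the time they emerge", but it ties identification to the monitoring. The ReMinder rule governs contact that nobody has requested. The two can be read together.

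**Conclusion.** The point holds as a conflict between the abstract and the methods, with a modest analytic consequence. The abstract's start at discharge cannot occur: allocation comes up to 2 months after the hospital visit or discharge, or after the whole inpatient rehabilitation stay with no stated limit. The trial therefore estimates the effect of case management offered from that later point, with month 0 at different stages of recovery. This does not threaten the validity of the comparison between arms.

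The timing follows directly from the text and needs no assumption. The precision figure, about 3 to 7 of 146 participants, rests wholly on the assumed 2–5% of residual variance and on the plan's R of 0.5. It could be smaller if baseline HADS already captures recovery stage. The correction should be made because it sets the scope of the claim and costs almost nothing.

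**What to change.** 1. In the abstract and in the trial's conclusions, define the intervention as case management from randomisation, after the post-discharge or post-rehabilitation baseline visit.
2. Enter time from injury to baseline and discharge destination (home or rehabilitation centre) in the HADS model as prespecified fixed baseline covariates, kept whatever their significance.
3. Report by arm the time from injury and from discharge to randomisation. In the case-management arm, also report the time to first contact, taken from the case managers' registrations that the process evaluation already collects.

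The cost is some rewording and two degrees of freedom, with time from injury entered as a linear term. Injury date, length of hospital stay and destination are already recorded. The date of leaving rehabilitation is not listed among the recorded items and may have to be noted at the baseline visit. Nothing in this changes care or the rules for contact, and the stated scope of the trial becomes slightly narrower.

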**Discussion:**

At the moment, there is no integrated health care service for people with acquired brain injury and their family members in the long term. If case management is shown to be feasible and (cost)-effective, it could bridge the gap between patients’ and families’ needs and the available services.

**Trial registration:**

Netherlands Trial Register NL8104. Registered on 22 October 2019.

## Administrative information

The order of the items has been modified to group similar items (see http://www.equator-network.org/reporting-guidelines/spirit-2013-statement-defining-standard-protocol-items-for-clinical-trials/).

## Introduction

### Background and rationale {6a}

Acquired brain injury (ABI) may result from stroke (e.g. ischemic or haemorrhagic disruption of blood flow), traumatic brain injury (e.g. from a fall or a blow to the head), brain disease or hypoxia (e.g. after cardiac arrest or near-drowning). People with ABI often experience physical, communicative, cognitive, emotional or behavioural problems [1–3]. The persisting nature of these changes poses day-to-day challenges in a variety of life domains, such as work or education, household, social relationships and leisure [4–6], affecting not only quality of life of people with ABI but that of family members as well, as they may need to take on the role of caregiver [3, 7, 8]. There are ample health care services available for people with ABI, but problems exist with regard to their continuity, accessibility and timing [9–11]. People with ABI and family members feel ill-prepared for discharge from the hospital or rehabilitation centre and ‘abandoned’ once at home, being left with unmet health, social and vocational needs in the long term [10, 11].

The importance of supporting a changed life after ABI is increasingly recognized in clinical guidelines [12, 13]. Since there are relatively few methodologically sound studies evaluating longer-term care, the Action Plan for Stroke in Europe and the World Stroke Organization state that the development and evaluation of a ‘seamless, coordinated chain of support’, which includes life after ABI, is a development and research priority [14, 15].

The development and research on longer-term care services for ABI falls behind in comparison to populations where the need for long-term support has been recognized for longer, such as dementia, oncology and diabetes. A form of longer-term support for these populations is case management, which focusses on supporting people to adapt to the consequences of their health condition in daily life [16–20]. Case management promotes self-management, which refers to choosing strategies, making decisions and undertaking activities to manage a long-term condition and its consequences [21]. Case management varies in form and duration. The key element is a professional, the case manager, who serves as a first point of contact for patients and their family, is familiar with their situation, supports independent living and links them to available services in the community [22]. Case management has a positive impact on well-being in dementia, oncology and diabetes, reducing anxiety and depression and increasing quality of life [16–20]. It may decrease financial strains on healthcare as well; for dementia, costs were reduced by 22–33% when providing case management compared to care as usual [23].

Case management for ABI has been described in the literature, and commonly involves engagement, assessment, planning, education, training and skills development, emotional and motivational support, advising, coordination and monitoring [24]. These elements are based on best practice; to the best of our knowledge, no randomized controlled trials on long-term case management for ABI have been undertaken to date. The evidence base so far is weak, with a few relatively old non-randomized studies on case management for traumatic brain injury of too low a quality to draw conclusions on its effectiveness [25–29]. Long-term follow-up did show a positive effect on social activities and depression in stroke in a non-randomized trial [30] and short-term transitional care interventions also show promising results [31, 32]. However, since learning how to live with ABI is a dynamic process with fluctuating needs over the course of several years, 3 to 6-month follow-up in the first year and annual reviews hereafter are necessary [14]. A methodologically sound investigation of the feasibility and effects in terms of health and costs of such long-term support is called for [14, 15]. This article describes the study protocol for a pragmatic randomized controlled trial on long-term case management (18–24 months) for people with ABI and their family.

